**Sample size Determination**

Sample size for detecting the impact of the interventions on VMMC uptake

Unpublished data from an on-going demand creation study and an HIV community based study show an average of 30% circumcision prevalence in the target group (25-39 years); a corresponding refusal rate of 15% and loss to follow-up of 15%. Using an average MC uptake of 30%, an intra-cluster correlation coefficient (ICC) of 0.005, and a design effect of 2.5 in sample size formula for cluster studies, we estimated that in order to be able demonstrate at least a 33.3 % increase in the rate of VMMC among young adult men in intervention arms when compared to those in control arm with 80% statistical power, and Bonferroni adjusted two-sided $\alpha=(\frac{0.05}{3})=0.017$ following the implementation of study interventions , we will need a sample size of 4,932 men reached with the intervention.

The graph below (*Figure 1)* shows that an effect size equal to 33.3% increase in MC from 30% to 40% will require about 1233 participants per study arm (total 4932), while an effect size equal to 50% increase in VMMC from 30% to 45% will require 573 participants per study arm (total 2292).

Adjusting for refusal rate of 15% and a loss to follow up of 15%, suggests contacting 1603 per study arm resulting in a total of 6412 uncircumcised men aged 25-39 years.

Fig.1 shows a range of sample size requirements for detecting various percentage increases (effect sizes) in VMMC uptake due to the interventions assuming causal effect, and for an 80% power, a 1.7% significance level and a two sided test.

[figure not shown]

Figure 1: Sample Size Vs Percentage Increase in MC Uptake

Selection of Clusters (Locations):

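### The contact target of 1,603 per arm multiplies by 1.30 where it should divide by retention, and separately the ICC of 0.005 and the design effect of 2.5 are stated together with nothing that links them

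*Protocol*

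**What the plan says.** All the inputs are in the protocol under Sample size Determination. The test is set out "with 80% statistical power, and Bonferroni adjusted two-sided $\alpha=(\frac{0.05}{3})=0.017". Clustering enters through two numbers given side by side: "Using an average MC uptake of 30%, an intra-cluster correlation coefficient (ICC) of 0.005, and a design effect of 2.5 in sample size formula". No cluster size or size variation connects them.

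The results are "increase in MC from 30% to 40% will require about 1233 participants per study arm (total 4932") and, for the larger effect, "increase in VMMC from 30% to 45% will require 573 participants per study arm (total 2292").

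The step from men needed to men contacted is: "Adjusting for refusal rate of 15% and a loss to follow up of 15%, suggests contacting 1603 per study arm", or 6,412 in all. Table 5 spreads that total over the 45 Locations and turns it into 25,640 households and 209 villages. The HIV sub-study uses a design effect of 2.5 again, for 163 men per arm.

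**The concern.** A contact target should return the required number once the expected losses are taken off. Multiplying by one plus the loss rate does not do that, and with losses near 30% the gap is not negligible. The figure matters because Table 5 sizes the household and village sampling from 6,412, and 4,932 is carried forward as the expected number of participants.

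The clustering inputs raise a different question. An ICC and a mean cluster size determine the usual design effect, so quoting an ICC and a design effect that do not follow from each other leaves it unclear which assumption the trial is powered under. The ICC could be dropped from the sentence without changing any figure in it.

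**Working it through.** **Reproducing the plan's figures.** Inputs from Sample size Determination: 30% against 40%, two-sided alpha 0.017 (z = 2.387), power 80% (z = 0.842).

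- Uncorrected: n0 = [2.387 x sqrt(2 x 0.35 x 0.65) + 0.842 x sqrt(0.30 x 0.70 + 0.40 x 0.60)]^2 / 0.10^2 = 472.8.
- With continuity correction: n = (n0/4) x [1 + sqrt(1 + 4/(n0 x 0.10))]^2 = 492.6, rounded up to 493.
- 493 x 2.5 = 1,232.5, so 1,233. Without the correction, 473 x 2.5 = 1,182.5, which does not match.
- For 30% against 45% the same steps give 229, and 229 x 2.5 = 572.5, so 573.
- HIV sub-study: 2.5 x 1.96^2 x 0.216 x 0.784 / 0.10^2 = 162.6, so 163.

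All three figures use 2.5 as a fixed multiplier. The ICC is not needed for any of them.

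**Contacts.**

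- Plan: 1,233 x 1.30 = 1,602.9, so 1,603; 4 x 1,603 = 6,412.
- Sequential losses: retention 0.85 x 0.85 = 0.7225. Yield 1,603 x 0.7225 = 1,158 per arm, 6,412 x 0.7225 = 4,633 in total. Needed: 1,233/0.7225 = 1,707 per arm, 6,828 in total.
- Both losses taken on men contacted: retention 1 - 0.30 = 0.70. Yield 1,603 x 0.70 = 1,122 per arm, 6,412 x 0.70 = 4,488 in total. Needed: 1,233/0.70 = 1,762 per arm, 7,048 in total.
- Shortfall against 1,233: 75 men (6%) or 111 men (9%) per arm.

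**Power at design effect 2.5, equal arms, alpha 0.017.**

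| Men analysed per arm | n / 2.5 | Continuity-corrected | Uncorrected |
|---|---|---|---|
| 1,233 | 493 | 80.1% | 81.9% |
| 1,158 | 463 | 77.0% | 79.1% |
| 1,122 | 449 | 75.4% | 77.6% |

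**Design effect from the stated ICC.**

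- Mean Location size: 4,932/45 = 109.6. Design effect: 1 + (109.6 - 1) x 0.005 = 1.54.
- Size needed for 2.5 at ICC 0.005: (2.5 - 1)/0.005 + 1 = 301 men per Location.
- ICC needed for 2.5 at 109.6 men: (2.5 - 1)/108.6 = 0.0138.
- At 573 and 163 men per arm (11.25 Locations per arm) the mean sizes are 50.9 and 14.5, giving 1.25 and 1.07.

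**Unequal Location sizes.** With the Table 5 contacts, design effect = 1 + (sum m^2 / sum m - 1) x 0.005. The entries as read sum to 6,410 with sum of squares 2,274,280, so sum m^2 / sum m = 354.8.

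- Pooled at contacted size: 2.77. Scaled to the analysed size (x 1,233/1,603): 2.36.
- Without West Kolwa (1,223 contacts): 1.75 and 1.57.
- By arm, using the Table 3 allocation, at analysed size: IPC 1.48, Control 1.57, IPC+DSO 1.61, DSO 3.68.
- With the same size variation (CV 1.22) at 573 and 163 men per arm: 1.63 and 1.18.

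**Contacts by arm from Tables 3 and 5.** Control 1,281, IPC 1,252, DSO 2,421, IPC+DSO 1,456. At retention 0.7225 these leave about 926, 905, 1,749 and 1,052; at 0.70, about 897, 876, 1,695 and 1,019.

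**The case against.** Three points can fairly be made for the plan.

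First, 2.5 is defensible. The pooled Table 5 sizes at ICC 0.005 give 2.36 to 2.77, which bracket it. A reader might therefore go too far in concluding that 0.005 cannot produce 2.5; that holds only for equal Locations or arm by arm. What remains is that the protocol does not give this reasoning, that the pooled value rests almost wholly on one Location, that no single arm is near 2.5, and that the same 2.5 is used at sample sizes where neither calculation approaches it. It reads as a fixed assumption, and it is unexplained.

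Second, a reader might infer that the mismatch leaves the trial underpowered, or that it helps cause the contact shortfall. Neither follows. At mean Location size 2.5 is larger than 1.54, so the choice is conservative: at 1.54, 1,158 men per arm would still give about 95% power. The shortfall comes from the 1.30 step alone.

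Third, 6,412 is a planning figure and not a cap. Phase 1 lists every household in the selected villages, and all eligible men found there are to be approached, so the true yield could fall on either side. That limits the practical effect but does not make the stated arithmetic right.

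It is also tempting to treat 1,707 as the one correct figure. The protocol does not say whether the second 15% applies to men contacted or to men who agree, so 1,762 is equally open.

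**Conclusion.** Both points stand, separately.

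The inflation step is an arithmetic error. On the protocol's own loss rates, 1,603 contacts per arm yield 1,158 or 1,122 men, 6% to 9% below the required number, and neither reading of the losses rescues 1,603. The cost is about 3 to 5 percentage points of power. That size assumes the plan's design effect of 2.5 and equal arms. Equal arms are not what Table 5 plans, so 77% or 75% measures the error in the stated calculation and does not describe any actual comparison.

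The ICC and design effect are an unresolved pair of inputs. Depending on which one is believed, with equal arms and after the shortfall, power is about 75% to 77% (2.5) or about 94% to 95% (1.54, equal Locations), continuity-corrected. The documents do not support calling this evidence of underpowering. They do support saying that a reader cannot tell what clustering assumption the trial rests on.

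**What to change.** 1. **Contacts.** State whether the two 15% losses are sequential or both taken on men contacted, and divide by the matching retention: 1,707 per arm (6,828 in total) or 1,762 per arm (7,048 in total). That is 416 or 636 more contacts; at Table 5's ratio of about four households per contact (25,640/6,412), roughly 1,660 or 2,540 more households.
2. **If 6,412 is kept,** restate the expected analysable number and the power for each comparison with control, using the Table 5 contacts by arm (Control 1,281, IPC 1,252, DSO 2,421, IPC+DSO 1,456) and not an equal 1,603. This needs no extra men, only wording and a less favourable figure.
3. **Clustering.** State one ICC with its source, derive the design effect from the planned Location sizes including their variation, and restate power on that basis. If 2.5 is meant to absorb unequal sizes, say so, and show how far it depends on West Kolwa. The cost is a short calculation and a sentence or two.

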**Methods:** We will employ cluster-randomized controlled design. Through elimination by factors such as proximity to circumcising communities, multi-ethnic urban populations, and geographical proximity to each other, 45 administration Locations in Nyanza Province have been selected and randomized into IPC implemented alone, DSO implemented alone, IPC and DSO implemented together and control. Under IPC, we will develop a Toolkit for Addressing Barriers and Facilitators to VMMC with messages that address barriers to and reinforce facilitators of VMMC, and engage behavioral counselors to deliver intervention massages that are custom-made to address participants’ specific issues; Under DSO, selected facilities, days and hours will be set aside to serve only men aged ≥25 years; these sites will be served by older, male providers only; Under Combined IPC and DSO, the effect of both interventions implemented together will be examined; and in the Control locations, no intervention will be implemented. Altogether, 4,932 men aged 25-39 years are expected to take up VMMC during the study period, which will take up to nine months.

For aim 2, we will collect blood samples from bleeding vessels of an estimated 700 men whose HIV status is unknown, and perform unlinked test for HIV at the KEMRI/CDC HIV Laboratory in Kisumu. For aim 3, we propose to extract from our procurement, stores and accounts records expenditures for demand creation and service delivery.

To augment this study, we will nest a sub-study (sub-study 4) in all the 45 study Locations and enroll approximately 720 men who are in stable sexual relationships, together with their partners, for post circumcision follow up visits to monitor the impact of involving female partners on time to resumption of sex post-surgery.

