# STUDY AIMS AND JUSTIFICATION

***Aim 1: Assess the rate of uptake of VMMC services by men aged 25-39 years exposed to Inter-Personal Communication (IPC) vs. Designated (older men only) Service Outlets (DSO) vs. IPC and DSO interventions combined vs. no intervention.***

Justification: Since Kenya launched VMMC in November 2008, IRDO has circumcised 241,145 men as at June 2013, aggregated by age as follows: 88% under 24 years, 12% 25-39 years, and 2% ≥40 years. IRDO’s performance is relatively better than the provincial rate, which stands at under 10%, a clear demonstration that creative strategies to create demand for VMMC among older men are urgently needed if the country is to experience the immediate benefit of VMMC on HIV incidence. We will register all participants coming for VMMC services at our sites and document their assigned arm and date of circumcision. At enrollment, we will capture the details of each participant enrolled in the study and enter them into a Participants Master Log (Appendix 14), which comprise of all enrolled participants at baseline. The details will include: participant’s 3 names, national ID number, age, location, village, telephone number (of the participant or close friend) and date of enrollment. At endline, we will extract program data on MC uptake among clients aged 25-39 years in non-study VMMC health facilities and triangulate with those registered in the Participants Master Log as having been circumcised. The purpose of this comparision is to capture study participants who may have been circumcised in non-study health facilities (further discussion is on page 41).

***Aim 2: Determine through testing of unlinked de-identified blood from bleeding vessels from surgical wound, the proportion of men whose HIV status is unknown who are HIV infected (Sub-study 1).***

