Recruitment Approach: Depending on participant’s availability, this phase can be conducted together with Phase 2 if the intervention tool (Appendix 6) has been approved, and done subsequent to verification of MC status; alternatively, another visit will be made if participants do not have time or if Appendix 6 has not been approved. If another visit is needed, we will visit every household with enrolled participants at a time when they are likely to be at home (with their spouses where applicable) to discuss VMMC using the demand creation tool (Appendix 16: *VMMC Demand Creation Tool kit*) as described in the next sub-section.

Participants in IPC or IPC/DSO Location will receive information on VMMC while those in DSO Locations will be informed about, and given directions to VMMC sites designated to older men. During consenting, participants will be informed that by consenting to be enrolled in the study, they are consenting to be assigned into one of the three intervention arms or control. Hence, by consenting to join the study they will also have consented to participating in the respective interventions. After delivering the intervention (whether at enrollment visit or a subsequent one), participants will be given a pre-designed referral coupon (Appendix 15: Referral Coupon) to take along when going for services. They will also be asked to memorize the serial number if possible. The RAs will be expected to return to the same households up to three times (within a period of three month) to reach those not found at home during the previous visit – this applies to both enrollment visit and the visit to deliver the intervention, if different from enrollment visit.

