Data from our VMMC programs that target older men in most (12/14) of the districts of Nyanza province inhabited by non-circumcising Luo community suggest that the prevalence of HIV among men taking up VMMC and who accept testing is 10.8%. These data also suggest that 23.6% of the men in the target age-group who accept VMMC decline HIV-testing. To be conservative, we assumed that the prevalence of HIV in this group of men is around two times that of similar men who accept such testing, translating into 21.6% HIV prevalence among uncircumcised men whose HIV status is unknown. If our assumption of twice the prevalence is wrong, we believe we shall have erred on the side of safety - we shall have erred on the side of over-estimating rather than underestimating the required sample size thus ending up with a bigger sample size than would have needed. However, we will benefit immensely in terms of precision of the study estimates. Using a design effect of 2.5 due to clustering, in the sample size for estimating prevalence^41^, we estimated that we will need to test randomly selected unlinked blood samples from 163 men per arm whose HIV status is unknown in order to estimate a HIV prevalence that falls within 10% points of the true population prevalence with 95% confidence. Our study staff will collect samples from all of men who refuse testing but consent to Unlinked HIV testing. Binkin et al. (1992)^41^ found that for a relatively common disease (as is HIV in the study area), if the desired level of precision is around ±10% points or less and the design effect is around 2, then collecting data from more than 30 clusters provides good estimates of the true (unknown) population parameters with the desired level of precision. Our study will be conducted in 45 clusters.

With a refusal rate of 23.6% voluntary HIV testing, and a consenting rate of 60%, then the rate of getting a man who refuses testing but consents to the testing of unlinked blood sample from his bleeding vessels is 14.2%.   In other words, of the 4932 participants in the main study we expect 1164 (4932*0.236) to refuse HIV testing. With assumed unlinked HIV testing acceptance rate of 60%, we can obtain 700 such men from our sample size of 4932 in the main study. For a design effect of 2.5, using a sample size of 700 for the sub-study will enable us to estimate the HIV prevalence of 21.6% with a precision of  4.8%=sqrt[(2.5*1.96^2*.216*.784)/700].

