## Data Analysis:

***Aim 1:*** ***Compare the rate of uptake of VMMC services by men aged 25-39 years exposed to Inter-Personal Communication, Designated Service Outlets, and IPC+DSO.***

The main outcome measure of this study is VMMC uptake. To assess the rate of uptake of VMMC services by uncircumcised men aged 25-39 years, we will compare the proportion of men who accept to be circumcised across the intervention arms. Specifically, the proportion of men accepting to be circumcised in each of the three arms will be compared to the proportion accepting circumcision in the no intervention group. P-values will be adjusted for multiple comparisons using the Bonferroni method. In order to take into account the clustered nature of the data, we shall also employ statistical methods suitable for analysis of cluster-randomized trials, namely the multi-level logistic regression model via the generalized estimating equations (GEE) approach with a random intercept. The random intercept term will represent the differences in true log-odds between the Locations. Odds ratio of VMMC uptake comparing intervention groups to the control group with the same underlying uptake rate will be estimated. This model will simultaneously assess individual-level and Location-level factors associated with uptake of VMMC as well as the effect of the interventions. Most importantly, it will enable the assessment of the intervention at the level at which randomization occurred: the Location level.

As outlined above under Phase 4, we shall conduct an endline survey in all households with men aged 25-39 years to establish the post-intervention MC uptake, and for those circumcised, collect information on when and where they were circumcised. These will be compared with similar data collected at baseline, using the methods described in the paragraph above. In addition, we shall extract from our database information on age of participants receiving services in each Location/Cluster. We will also have a sense of effectiveness of each recruitment strategy from surrendered referral coupons and from responses to question 1 in Appendix 20 B, asked to men who come for MC and through Appendix 2, the number of men reported and/or verified as circumcised at endline. This information, collected from multiple sources and through multiple approaches, will be compared across different arms of the study.

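### The 4,932 men are the analysable denominator for four arms, but the abstract states them as expected circumcisions and the HIV-testing sub-study uses them the same way; at the plan's own rates about 1,850 circumcisions and 262 samples follow, not 4,932 and 700

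*Protocol*

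**What the plan says.** The number 4,932 appears in three roles.

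- Protocol, Abstract (Methods): "Altogether, 4,932 men aged 25-39 years are expected to take up VMMC during the study period". This is a count of men circumcised.
- Protocol, Sample size Determination: "we will need a sample size of 4,932 men reached with the intervention". The next paragraph says that raising uptake from 30% to 40% "will require about 1233 participants per study arm (total 4932"). This is a count of men over four arms, one of them control. The section then inflates 1,233 to 1,603 per arm (6,412 in total) for 15% refusal and 15% loss to follow-up.
- Protocol, HIV testing of participants with unknown HIV status: "of the 4932 participants in the main study we expect 1164 (4932*0.236) to refuse HIV testing". The same section gives the 23.6% as the share declining HIV testing among men of the target age who accept circumcision. It assumes that 60% of decliners consent to unlinked testing, and so arrives at 700 samples and a half-width of 4.8 points. It also sets a requirement of 163 samples per arm for a precision of 10 points.

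The figure of 700 recurs in the Abstract and in the sub-study's Methods/Procedure.

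**The concern.** A denominator and an event count differ by the uptake proportion, which the plan puts at 30% to 40%. If 4,932 is the denominator, the abstract promises far more circumcisions than the design can produce. The error also enters a calculation. Sub-study samples are taken at circumcision surgery, so only circumcised men can contribute. Starting from 4,932 instead of the number circumcised overstates the expected decliners, the sample yield and the precision. At stake are a headline planning figure and whether the sub-study can meet its own per-arm precision target.

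**Working it through.** **Inputs.** From Sample size Determination: uptake 30% in control and 40% with intervention, two-sided alpha 0.017, power 80%, design effect 2.5, four arms. From the HIV-testing sub-study: 23.6% decline testing, 60% of those consent to unlinked testing, assumed prevalence 21.6%, design effect 2.5.

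**Step 1: what 4,932 is.** The two-proportion formula is n = [z(1−α/2)·√(2p̄q̄) + z(power)·√(p₁q₁ + p₂q₂)]² / (p₂ − p₁)². With p₁ = 0.30, p₂ = 0.40 and α = 0.017 it gives 473 per arm, or 493 with the continuity correction. Then:

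- 493 × 2.5 = 1,232.5, rounded up to 1,233 per arm
- 1,233 × 4 = 4,932, exactly the stated total
- the 30% versus 45% case also reproduces: 229 × 2.5 = 572.5, stated as 573
- 1,233 × 1.30 = 1,602.9, stated as 1,603; 1,603 × 4 = 6,412

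So 4,932 is the number of analysable men in four arms, after refusal and loss to follow-up. It is not a count of circumcisions.

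**Step 2: expected circumcisions among 4,932 men.**

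- Control: 1,233 × 0.30 = 369.9
- Each intervention arm: 1,233 × 0.40 = 493.2
- Total: 369.9 + 3 × 493.2 = 1,849.5, about 1,850
- Ratio: 4,932 / 1,849.5 = 2.67
- Range: 4,932 × 0.30 = 1,480 if every arm stays at 30%; 4,932 × 0.40 = 1,973 if every arm reaches 40%

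**Step 3: the sub-study as written.** 4,932 × 0.236 = 1,164 decliners, and 1,164 × 0.60 = 698, stated as 700. Half-width = √(2.5 × 1.96² × 0.216 × 0.784 / 700) = 4.8 points. The per-arm requirement is 2.5 × 1.96² × 0.216 × 0.784 / 0.10² = 162.6, stated as 163. All of these reproduce.

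**Step 4: the sub-study from circumcised men.**

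| Quantity | As stated | From 1,850 circumcised |
|---|---|---|
| Decline testing | 1,164 | 1,849.5 × 0.236 = 436 |
| Give samples | 700 | 1,849.5 × 0.236 × 0.60 = 262 |
| Pooled half-width | 4.8 points | √(2.5 × 1.96² × 0.216 × 0.784 / 262) = 7.9 points |
| Samples, control arm | 163 needed | 369.9 × 0.236 × 0.60 = 52 |
| Samples, each intervention arm | 163 needed | 493.2 × 0.236 × 0.60 = 70 |

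To obtain 163 samples in one arm, 163 / (0.236 × 0.60) = 1,151 men would have to be circumcised there. That is 1,151 / 1,233 = 93% uptake, against the planned 30% or 40%.

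**The case against.** The main defence is that the abstract contains one loose sentence, while the sample size reproduces and the power of the main comparison is untouched. That stands for the main comparison. It does not dispose of the point, because the sub-study's 700 samples and 4.8 points depend on the same substitution.

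One could also say that 4,932 is net of losses, so more circumcisions would come from the larger number of men contacted. Even if all 6,412 contacted men took up at the planned rates, 1,603 × (0.30 + 3 × 0.40) = 2,404.5 circumcisions would follow, about half of 4,932.

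On precision, a pooled half-width of 7.9 points still meets the 10-point target. A design effect that fell with fewer samples per Location would narrow it further. Both remarks are fair. The first does not rescue the per-arm target, and the second does not restore the number of samples.

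A stronger reading is tempting. The sample size speaks of men reached, and the Data Analysis section heads Aim 1 "Compare the rate of uptake of VMMC services by men aged 25-39 years exposed to Inter-Personal Communication". Delivery may follow enrolment, with a limited number of return visits. A reader might infer that the comparison is confined to men who received the intervention, which would remove hard-to-reach men from the intervention arms only. The documents do not support this:

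- The total includes 1,233 control men, so the phrase cannot be literal.
- Refusal and loss are applied to every arm.
- The Data Analysis text compares proportions by arm, with no restriction to men reached.
- Endline works from the "Participants Master Log (Appendix 14), which comprise of all enrolled participants at baseline".
- No rate of non-delivery is given, so any bias or error rate would rest wholly on assumed values.

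**Conclusion.** The point holds as an inconsistency in stated figures with a concrete consequence. The abstract's expected number of circumcisions is about 2.7 times too high: about 1,850 at the planned rates, and between 1,480 and 1,973 if all arms sit at 30% or all at 40%. The sub-study's yield is overstated by the same factor: about 262 samples rather than 700, with a half-width of about 7.9 points rather than 4.8. Its requirement of 163 per arm is out of reach at 52 to 70.

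These results use only the plan's own uptake, refusal, consent, prevalence and design-effect values, and equal arms of 1,233. The main sample size is sound on those inputs. The finding does not show a biased primary analysis: the wording about men reached or exposed is loose, but no analysis text turns it into a restricted denominator.

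**What to change.** - **Abstract:** state about 1,850 circumcisions expected among 4,932 analysable men, at 30% uptake in control and 40% in the three intervention arms.
- **Sample size Determination:** describe the 4,932 as analysable men across the four arms, after refusal and loss to follow-up. Do not relabel them as men enrolled, because the figure is already net of both. If refusal is taken to fall before enrolment and loss after it (an assumption), enrolled men would number about 1,603 × 0.85 = 1,363 to 1,233 × 1.15 = 1,418 per arm.
- **HIV-testing sub-study:** apply the 23.6% and 60% to the number circumcised, and restate decliners, samples and half-width. Carry the result to the 700 in the Abstract and in Methods/Procedure. Then either present the sub-study as one pooled estimate or show how 163 samples per arm could be reached.

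The cost is wording and a short recalculation. The main sample size and the randomisation do not change. The visible price is a smaller headline number of circumcisions and a less precise sub-study.

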2. Separating eligible from ineligible Locations: To ensure the populations in participating Locations are as homogenous as possible in terms of ethnicity (which defines circumcising and non-circumcising communities), we spread the map on a flat surface and systematically identified and excluded 37 Locations: 34 bordering traditionally circumcising communities in Kuria, Gucha, Central Kisii, Nandi, Vihiga, Butere-Mumias and Busia districts, and 3 within cosmopolitan Kisumu city where mixed ethnic communities live. In addition, we excluded 5 Locations in the islands due to poor access. Consequently, we remained with 122 eligible Locations to select from (Fig 2: Map 2).
3. Selecting participating Locations: Of the remaining 122 eligible Locations, we randomly selected the starting point and went through the process of systematically selecting each Location and excluding all the contiguous ones until we identified the maximum possible Locations that did not share a boundary. This exercise was done repeatedly by randomly selecting different Locations as the starting point and seeing how many Locations we ended up with. The goal was to select the highest number while ensuring none is proximal to each other. Based on these selection criteria, 45 was the maximum number of Locations that could be included in the study (Fig. 2: Map 3).
4. Random assignment of participating Locations: The names of the 45 Locations were compiled and submitted to the study Biostatisticians (FO & VS) for randomization.The names were entered into Stata V12 statistical package and a randomization schedule produced using the random-number generator. Using simple randomization to allocate clusters, roughly equal number of Locations (11-12 per arm) was allocated to each of the four study arms (Fig 2: Map 4).

A summary of the steps and the number of locations are shown in *Table 1* below while randomization and distribution of allocation to the study arms by districts are shown in Tables 2 and 3.

**Table 1:** Summary of Selected Study Locations

| **Total Locations in *Luo* Nyanza Province** | 233 |
| --- | --- |
| Locations where IRDO is providing VMMC services | 194 |
| Locations excluded because of an ongoing pilot demand creation study | 30 |
| Locations excluded because they border traditionally-circumcising communities | 34 |
| Locations excluded because of having a multi-ethnic population | 3 |
| Locations excluded because of poor accessibility (Islands) | 5 |

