| Locations eligible for selection | 122 |
| Locations excluded because they are proximal to a previously selected Location | 77 |
| Number of Locations selected for the study | 45 |

**Table 2:** The number of Locations assigned to each study arm by district

|  | **Study Arm** | | | | **Total** |
| --- | --- | --- | --- | --- | --- |
| **District** | **Control** | **IPC** | **DSO** | **IPC+DSO** |  |
| Bondo | 1 | 1 | 1 | 1 | 4 |
| Homabay | 1 | 1 | 2 | 1 | 5 |
| Ndhiwa | 1 | 1 | 2 | 1 | 5 |
| Kisumu East | 1 | 0 | 2 | 1 | 4 |
| Kisumu West | 1 | 1 | 0 | 1 | 3 |
| Nyatike | 1 | 2 | 1 | 2 | 6 |
| Migori | 1 | 0 | 0 | 1 | 2 |
| Rarieda | 1 | 1 | 0 | 0 | 2 |
| Rongo | 0 | 1 | 0 | 2 | 3 |
| Siaya | 1 | 2 | 1 | 2 | 6 |
| Suba | 2 | 1 | 2 | 0 | 5 |
| Totals | 11 | 11 | 11 | 12 | 45 |

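### Allocation is called simple randomisation, but the printed 11/11/11/12 split and its even district spread hardly fit that; the procedure should be stated and a random district intercept added.

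*Protocol*

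**What the plan says.** Protocol, Selection of Clusters (Locations), step 4: the 45 Location names were entered in Stata and "a randomization schedule produced using the random-number generator". The step then reads: "Using simple randomization to allocate clusters, roughly equal number of Locations (11-12 per arm) was allocated to each of the four study arms". It mentions no fixed arm sizes, blocks, strata or re-drawing.

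Table 2 ("The number of Locations assigned to each study arm by district") prints 11 Locations each for Control, IPC and DSO and 12 for IPC+DSO, over 11 districts. Table 3 lists the allocation Location by Location.

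Data Analysis, Aim 1, describes a multi-level logistic model. Of its clustering term it says: "The random intercept term will represent the differences in true log-odds between the Locations". It adds: "This model will simultaneously assess individual-level and Location-level factors associated with uptake of VMMC as well as the effect of the interventions". Those factors are not named, so district is neither included nor ruled out.

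**The concern.** Simple randomisation assigns each Location independently, so arm sizes vary by chance and districts are not balanced. The printed schedule is close to level on both counts. The described procedure and its printed result therefore do not fit together, and a reader cannot tell which restrictions were applied.

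This bears on the analysis. When arms are nearly even within districts, differences between districts largely cancel out of the arm comparisons. If district is not in the model, those differences still count as between-Location variance. Standard errors are then larger than they need be, and the test is conservative. How much is lost depends on how far districts differ in uptake.

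**Working it through.** **Printed allocation.** Counting Table 3 by arm and district gives Table 2 in every cell, with totals 11/11/11/12.

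**Arm sizes under simple randomisation.** The probability of this split, in any order of arms, is 4 × 45! / (11!³ × 12!) / 4⁴⁵ = 0.0127, or about 1.3%.

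**Evenness by district.** The measure is the sum of squared cells of Table 2; smaller means more even.
- Observed: 65.
- Smallest possible with these district sizes: 59. The excess of 6 comes from Kisumu East ("Kisumu East | 1 | 0 | 2 | 1 | 4": 6 against 4), Rongo (0/1/0/2: 5 against 3) and Suba (2/1/2/0: 9 against 7). The other eight districts are as even as their size allows.
- Expected under simple randomisation: the sum over districts of n(n−1)/4 + n = 160/4 + 45 = 85.

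Exact convolution over the 11 districts gives P(split 11/11/11/12 and sum of squares ≤ 65) = 3.75 in 100,000. With arm totals fixed at the printed values, P(sum of squares ≤ 65) = 0.0000375 / 0.0127 = 0.003. Other evenness measures put the joint probability between about 3.5 and 38 in 100,000.

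**Effect of leaving district out.** Inputs: the protocol's 4,932 men over 45 Locations, so m = 109.6 per Location; α = 0.05/3 = 0.0167 per comparison; and two ICC values. The protocol states "an intra-cluster correlation coefficient (ICC) of 0.005, and a design effect of 2.5 in sample size formula for cluster studies". These two figures do not agree at this cluster size, since 1 + 108.6 × 0.005 = 1.54. Both are therefore used: 0.005, and (2.5 − 1)/108.6 = 0.0138. The share f of between-Location variance that lies between districts is not in the protocol; 30% and 50% are assumptions.

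For an arm compared with control, with k = 1/n_arm + 1/n_control, v_b = ICC and v_w = (1 − ICC)/m (in units of the outcome variance):
- variance if district is ignored: k(v_b + v_w)
- actual variance: k[(1 − f)v_b + v_w] + f·v_b·S, where S is the sum over districts of the squared difference between the arm's and control's shares of their Locations in that district.

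For IPC against Control, six districts differ by one Location, so S = 6/121 = 0.0496 and k = 2/11 = 0.1818. At ICC 0.005 and f = 0.5, v_w = 0.995/109.6 = 0.00908. The first variance is 0.1818 × 0.01408 = 0.00256. The second is 0.1818 × 0.01158 + 0.0025 × 0.0496 = 0.00223. The standard error is overstated by √(0.00256/0.00223) ≈ 1.07, about 7%.

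Error and power below come from simulating a Location-level analysis on the printed allocation, with the effect set to give 80% power when district carries nothing. Gains are upper figures because the variance components were taken as known.

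| ICC | District share | SE overstated | True error (nominal 1.7%) | Power without district | Gain with random district intercept |
|---|---|---|---|---|---|
| 0.005 | 30% | 3-4% | 1.3-1.5% | 81-83% | up to about 3 points |
| 0.005 | 50% | 5-7% | 1.1-1.2% | 81-82% | up to about 5 points |
| 0.014 | 30% | 5-7% | 1.0-1.3% | 81-82% | up to about 5 points |
| 0.014 | 50% | 9-13% | 0.8-1.0% | 82-83% | up to about 9 points |

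If district carries nothing, a random district intercept loses essentially no power. Fixed district effects would lose about 5-8 points.

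**The case against.** The strongest reply is that this is loose wording. Sorting the 45 names by a random number and cutting the list into four fits the text of step 4 and gives 11/11/11/12 every time. The same sentence openly reports 11-12 per arm. Simple may just mean unstratified, and fixing arm sizes widens no interval. This stands: the arm split alone does no harm.

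A reader might go further and infer that allocation was stratified or re-drawn by district, that the model ignores this, and that the intervals are therefore too wide. The protocol does not support that chain. No text mentions district in the allocation. Three districts are less even than they could be, and the coordination regions are uneven (region 1 is 4/3/6/2 and region 3 is 2/3/1/5, in the order Control/IPC/DSO/IPC+DSO). The evenness measure was chosen after seeing the table. The model may also carry district among its unnamed Location-level factors, and a covariate list is commonly left to a statistical analysis plan, which is not at hand.

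A reader might also expect a larger loss by taking the district share as a share of the total variance of Location means. At ICC 0.005, true between-Location variance is only 0.005/0.01408 = 36% of that total, so a 30% share of it is about 11% of the total.

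Finally, any error is conservative, and the planned analysis keeps at least 80% power in every scenario shown. That also stands and limits the weight of the point. It does not remove the mismatch between the described procedure and the printed schedule, or the case for a cheap model term.

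**Conclusion.** The point holds in a limited form. The description as simple randomisation does not fit the printed schedule: about 1.3% for the arm split, and about 4 in 100,000 jointly with the district evenness, on a measure chosen afterwards. Arm sizes were very probably fixed. Use of district is suggested (p about 0.003 given the arm totals) but unproven.

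The consequence for the analysis is conditional. The printed allocation is nearly even by district however it arose, so leaving district out makes intervals somewhat too wide only if districts differ in uptake. With an assumed district share of 30-50%, the true error is about 1.1-1.5% at ICC 0.005 and about 0.8-1.3% at ICC 0.014, against 1.7% nominal. The power to gain is up to about 3-5 and 5-9 points respectively. With a share of zero there is no effect. Type I error is not inflated in any of these cases. The description would also define the reference set for a permutation test, but the protocol plans none, so no harm follows there.

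**What to change.** - **Selection of Clusters (Locations), step 4:** replace the reference to simple randomisation with the procedure recorded in the randomisation file. State how arm sizes were fixed, and whether district was used through stratification or re-drawing.
- **Data Analysis, Aim 1:** add district as a random intercept above Location, or as the stratum if the file shows that allocation was stratified.

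The cost is protocol wording and one model term, using district labels already printed in Table 3. With a random intercept, little or no precision is lost if district explains nothing. Fixed district effects are less attractive unless the file shows stratification, because they would cost about 5-8 points of power in that case.
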